10.3 Adjustment of Significance and Confidence Interval

A Bonferroni correction or false discovery rate (FDR) adjustment will be applied for multiple comparisons to control Type I error.

Results will be presented with 95% confidence intervals, and significance will be set at a two-tailed p-value of <0.05 after adjustments.

10.4 Sample Size Calculations

No formal power calculation has been conducted due to the pilot nature of the study. However, 40 participants (20 per group) were chosen based on feasibility and alignment with recommendations for exploratory trials in emerging therapies​.

Post-hoc power analysis will assess the adequacy of the sample size in detecting clinically meaningful changes in primary outcomes.

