4.3 Primary Endpoint

- **Safety:** Incidence of adverse events (AEs) and serious adverse events (SAEs) during the trial period.

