5.1 Overall Trial Design

- A Phase IIa, open-label, randomized controlled trial with two arms:

1. Active treatment arm; Two dosing sessions with psilocybin 25mg with psychological support alongside TAU.

2. Active comparator control arm; TAU only.

TAU includes specialized care offered in an eating disorder unit in Region Skåne, Sweden. If the active treatment arm is determined to be safe, tolerable, and preliminarily effective during the follow-up assessment, participants in the control group will have the option to switch to the active treatment while maintaining their usual specialized care.

This design minimizes ethical concerns regarding withholding a potentially effective treatment.

Participants will be randomly assigned (1:1) to either the intervention or control group.

Block randomization stratified by age group (16–17 and 18–35 years) will ensure balanced representation.

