**Statistical Consideration**

With only 40 participants, statistical power to detect between-group differences is limited regardless of blinding. Thus, the trial is appropriately focused on safety, feasibility, and tolerability. Qualitative and neurobiological measures are included to support interpretation.

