10.2 Statistical Analyses

This will be an open label, two-arm, active comparator (TAU; treatment as usual), , randomized controlled, between- and within-subjects, design in up to 40 completing patients meeting DSM-5 criteria for eating disorders. The patients will be randomly allocated to the psilocybin treatment-arm. The study analyses will enable comparison of efficacy between psilocybin-treatment and treatment as usual, as well as longitudinal within-patient efficacies.

- Primary Baseline Analyses:
  The primary analyses will involve descriptive statistics for demographic and baseline characteristics, ensuring comparability across groups, and control for follow-up measurements.
- Primary Endpoints analysis
- We will analyse differences in the number of participants and severity experiencing AE/SAE between the groups standardized forms for AE/SAE capturing: Event description, Start and end dates, Severity (e.g., mild, moderate, severe), Relatedness to intervention (assessed by safety review committee), Action taken.

The primary statistical methods will be:

- Descriptive Frequencies and Percentages.
- Comparing Proportions (Most Common for "Incidence") (Chi-squared test (or Fisher's Exact Test): Fisher's exact test is preferred for small cell counts (<5).
- Risk Ratio (RR) or Odds Ratio (OR) with Confidence Intervals: Report these measures of effect size to quantify the magnitude and precision of the difference between groups. An RR > 1 would indicate a higher risk in the intervention group.
- Comparing Severity and Relatedness is assessed with Mann-Whitney U test or Student t-test to compare severity distributions between groups.
- Secondary Endpoints:
  For secondary endpoints (e.g., changes in fMRI connectivity, BDNF, rating scales), group comparisons, including t-test, ANOVA, and Repeated Measures ANOVA will be utilized. When controlling for variables such as individual differences, ANCOVA or MANCOVA will be utilized. Principal component analysis (PCA) or independent component analysis (ICA) may be applied to identify patterns in fMRI data. Task-based fMRI data will be analysed using univariate models to investigate treatment effects in syndrome-related neural circuits (Celeghin et al., 2023; Bronleigh et al., 2022). Endpoints include longitudinal between- and within-person analyses.

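### Section 10.4 makes post-hoc power the test of whether the sample size was adequate; from observed rates it only restates the p-value, and at a fixed difference it belongs in the protocol now

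*Protocol*

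**What the plan says.** Section 10.4 states that "No formal power calculation has been conducted due to the pilot nature of the study" and that "40 participants (20 per group) were chosen based on feasibility". It then commits to a method for judging that number afterwards: "Post-hoc power analysis will assess the adequacy of the sample size in detecting clinically meaningful changes in primary outcomes".

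The primary endpoint in section 4.3 is "Incidence of adverse events (AEs) and serious adverse events (SAEs) during the trial period". Section 10.2 compares the proportions between arms by a chi-squared test or, for small cells, Fisher's exact test, and adds a risk ratio or odds ratio with confidence intervals. Under section 10.3, "significance will be set at a two-tailed p-value of <0.05 after adjustments", and results carry 95% confidence intervals. In section 5.1, under Statistical Consideration, the protocol already concedes that "With only 40 participants, statistical power to detect between-group differences is limited regardless of blinding".

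The protocol gives no meaningful difference in AE or SAE incidence, no expected control rate, no target power and no level of power that would count as adequate.

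**The concern.** A feasibility-based sample size is acceptable in a pilot. The difficulty is the method chosen to judge it. Apart from the general remark that power is limited, post-hoc power is the only assessment of sample-size adequacy in the protocol, and the sentence can be read in two ways.

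- **Power at the observed rates.** With no meaningful difference defined, the observed difference is the only effect size that the text supplies. Power computed from it carries no information beyond the p-value.
- **Power at a fixed meaningful difference.** This is a legitimate quantity, but it uses no observed effect. Left until the end of an open-label trial, the difference can be selected once the results are known.

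At stake is the conclusion about whether 40 participants could address the primary safety question. Neither version of post-hoc power says which AE or SAE rates the data rule out, and that is what a pilot safety trial needs to report.

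**Working it through.** **Inputs.** From the protocol: 20 per group (10.4), 1:1 allocation (5.1), two-sided 0.05 (10.3), binary primary endpoint (4.3), Fisher's exact test for small cells (10.2). Assumed, because the protocol gives none: an adequacy threshold of 80% (70% and 90% also tried), common AE rates of 5% to 90%, and the control rates in step 4. There is no stated power figure to reproduce.

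**1. Observed power as a function of p (normal approximation).** Observed power ≈ Φ(|z| − 1.960), where |z| is the value that gives the two-sided p.

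| p | Observed power |
|---|---|
| 0.001 | 91% |
| 0.0051 | 80% |
| 0.01 | 73% |
| 0.05 | 50% |
| 0.10 | 38% |
| 0.20 | 25% |
| 0.50 | 10% |

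The sample size does not enter once p is known. Reaching 80% needs |z| ≥ 1.960 + 0.842 = 2.802. With no true effect this has probability 2 × (1 − Φ(2.802)) = 0.0051, so observed power is below 80% in 99.49% of trials of any size. The corresponding figure is 98.70% for a 70% threshold and 99.88% for 90%. At a Bonferroni level of 0.025 with an 80% threshold it is 99.80%.

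**2. Exact check for the binary endpoint.** All 21 × 21 tables of 20 v 20 were enumerated. For each table, exact Fisher power was computed with the observed proportions taken as true. The highest value in any non-significant table is 49% (5/20 v 12/20, p = 0.054; its mirror image 8/20 v 15/20 gives the same).

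**3. No true difference, exact Fisher.** The probability that observed power is below 80% is 99.998% at a common rate of 5%, 99.94% at 10%, 99.67% at 20%, 99.66% at 30% and 99.76% at 50%, with the same values mirrored above 50%. Across 5% to 90% it is at least 99.6%. With a 70% threshold it stays above 99%. With the pooled z formula in place of Fisher, the lowest value at 80% is 99.34%.

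The measure also misleads when the design is sound: if true power is exactly 80%, observed power falls below 80% half the time.

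**4. Power at a fixed difference (exact Fisher, 20 v 20).** Control rates are assumptions.

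| Control rate | +20 points | +40 points | +45 points | +50 points |
|---|---|---|---|---|
| 5% | 30% | 82% | 89% | 94% |
| 10% | 24% | 74% | 84% | 91% |
| 20% | 19% | 65% | 76% | 85% |
| 30% | 16% | 60% | 73% | 85% |

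No trial result is needed for this table, so it can be stated in advance. The answer depends heavily on the difference and control rate chosen, which is why the choice should not wait for the data.

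**5. Precision with 20 dosed.** The exact upper limit for 0 events is 1 − 0.025^(1/20) = 16.8%. The Clopper-Pearson limits for 1 and 2 events are 24.9% and 31.7%.

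**The case against.** The strongest reply is that section 10.4 speaks of clinically meaningful changes, which most naturally means power at a meaningful difference. On that reading power does not restate the p-value, and the 99.6% figure does not apply. The analysis plan, which is not shown, might define the difference. This stands as a limit on steps 1 to 3, which hold only if observed rates are used. It does not rescue the sentence: power at a fixed difference is a design quantity, and calling it post-hoc leaves the choice open until results are visible.

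A reader might infer that the fixed-difference answer is already known and is that 40 participants are too few. The documents do not support that. Step 4 runs from 16% to 94% according to the assumed rates, and the protocol names neither a control rate nor a difference. The final number is not strictly 20 per arm either, because recruitment continues until at least 20 intervention participants have been dosed.

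A reader might also infer that a non-significant safety comparison will be explained away as underpowered. Nothing in the protocol says so. Sections 10.2 and 10.3 already plan confidence intervals, which will be reported whatever the power analysis shows, and section 5.1 is open about limited power. This part of the objection stands and reduces the harm.

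Finally, the sample size, tests and safety reviews do not use post-hoc power. That also stands.

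**Conclusion.** The point holds in limited form. Section 10.4 assigns the adequacy judgement to a method that cannot deliver it from observed rates. There, power is a restatement of p: at most 49% in any non-significant 20 v 20 Fisher table, and below 80% at least 99.6% of the time when the arms do not differ. These figures assume 20 per arm, two-sided 0.05 and, for the second, an 80% threshold that the protocol does not state; the conclusion is not sensitive to using 70% or 90%. If a fixed difference is intended, the calculation is valid but is placed at the wrong time and lacks its inputs.

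The documents do not support calling the sample size inadequate, or the primary safety analysis invalid. The consequence is modest and confined to what the final report may conclude about adequacy.

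**What to change.** Delete the post-hoc power sentence in section 10.4 and put a precision statement in its place, for example: with 20 dosed participants, the exact two-sided 95% upper limit for an event rate is 16.8% if no participant has the event, 24.9% if one does and 31.7% if two do; adequacy of the sample size will be judged by the width and limits of the 95% confidence intervals for AE and SAE rates and for the between-arm risk difference.

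This builds on the intervals already planned in sections 10.2 and 10.3, adding intervals for the rates themselves and for the risk difference alongside the risk ratio or odds ratio. If the sponsor also wants a statement about power, give it now as a range over named control rates and differences, as in step 4 of the working.

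The cost is one replaced sentence and two simple intervals. No further participants or data are needed, and no other analysis changes.

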10.5 Interim Analysis

Following two administration sessions of 25mg psilocybin, a panel of three senior psychiatrists, who are not part of the research team, will conduct an evaluation of the safety data and adherence to the protocol. This analysis will be repeated after a total of 20 psilocybin administrations have been completed. After 25 patients over 18 have been through dosing sessions, patients 16-17 will be recruited.

11. Quality Control and Quality Assurance

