Aim: To explore the safety, tolerability, and initial efficacy of psilocybin administered with psychological support compared to Treatment as Usual (TAU) in adolescents and young adults aged 16-35 with anorexia nervosa (AN).

Primary Objective: To assess the safety and tolerability of psilocybin 25 mg in this population.

Secondary Objectives: To evaluate the efficacy of psilocybin with psychological support in reducing AN symptom compared to TAU, investigate potential mechanisms of action through self-report questionnaires, neuroimaging and BDNF analysis, and conduct qualitative analysis of subjective experiences.

Trial Design: Open, randomized controlled trial with two arms: (1) two doses of psilocybin (25 mg) with psychological support with one month apart and alongside treatment as usual, and (2) Treatment as Usual (TAU).

Trial Population: Adolescents and young adults aged 16-35 diagnosed with anorexia nervosa.

Number of Subjects: 40 participants (20 per group).

Inclusion Criteria: Diagnosed with AN per DSM-5, aged 16-35, BMI >16, who have experienced at least one period of weight gain followed by weight loss.

Exclusion Criteria: Psychosis, bipolar disorder, substance use disorder, contraindicated medications, severe medical conditions, or metal contraindications for MRI.

Intervention: Two doses of 25 mg psilocybin with psychological support, or TAU. Psilocybin sessions will be accompanied by preparatory and integration sessions.

Investigational Medicinal Product Dosage Administration: Psilocybin 25 mg administered orally during supervised sessions.

Ethical Considerations/Benefit-Risk: Comprehensive safety monitoring, support during sessions, and procedures in place for managing any adverse events. First 25 participants included above 18 years of age, followed by 15 patients between 16-17 years of age. Safety review committee after first 10 psilocybin dosing sessions to review adverse events and protocol adherence. Literature on psilocybin clinical trials report low risk for adverse events and large gap in treatment options for patients with relapse in anorexia nervosa.

Planned Duration of the Trial: Q3 2025 – Q2 2027.

2. Background and Rationale

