9.5 Safety Review Committee

A Safety Review Committee will oversee trial safety and make recommendations on trial continuation. The committee will receive notification on all SAEs and SUARs by the research team within 24 hours.

The committee will review safety data quarterly and after every interim analysis (after every 10 psilocybin dosing sessions). They may recommend protocol modifications, halting recruitment, or terminating the trial based on emerging risks.

The committee will include at least two clinical and senior psychiatrists, a clinical pharmacologist, and a statistician, not affiliated with the research team, but not from an independent organisation.

No formal Data Monitoring Committee will be used in this trial.

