10.1 Analysis Population

- Both the Intention-to-treat (ITT) and per-protocol populations will be analysed.

ITT analysis will include all participants who are randomized, regardless of protocol adherence, to ensure generalizability.

Per-protocol analysis will focus on participants who completed the study as planned, ensuring the assessment of efficacy under ideal conditions.

The trial aims to dose at least 20 participants in the psilocybin treatment arm. This number refers to participants who receive at least one 25 mg psilocybin session, not only those who are randomized.

Analyses of safety and tolerability will primarily focus on this dosed cohort.

Recruitment will continue until a minimum of 20 participants in the intervention arm have received at least one dose, unless safety or feasibility concerns require early termination.

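### Section 10.5 admits 16-17-year-olds only after 25 adults have been dosed, but a 1:1 trial of 40 doses about 20 people; the synopsis sets a different entry condition

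*Protocol*

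**What the plan says.** **Entry of minors.** Section 10.5 (Interim Analysis): "After 25 patients over 18 have been through dosing sessions, patients 16-17 will be recruited". The synopsis, under Ethical Considerations/Benefit-Risk: "First 25 participants included above 18 years of age, followed by 15 patients between 16-17 years of age". The first counts adults dosed; the second counts adults included.

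**Size.** Section 10.4: "40 participants (20 per group) were chosen based on feasibility", the same figure as in the synopsis. Section 5.1 randomises 1:1, in blocks stratified by age group (16-17 and 18-35), and gives psilocybin to one arm, in two sessions. Sections 5.1 and 10.1 add a floor on dosed participants: "Recruitment will continue until a minimum of 20 participants in the intervention arm have received at least one dose".

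**Switch.** Sections 5.1 and 7.4 let control participants change to psilocybin after their six-month follow-up if the safety committee is satisfied. Section 15 leaves the switch out of what counts as study completion for reporting.

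**Safety reviews.** Synopsis: "Safety review committee after first 10 psilocybin dosing sessions to review adverse events and protocol adherence". Section 9.5: "The committee will review safety data quarterly and after every interim analysis (after every 10 psilocybin dosing sessions"), by a committee that includes a pharmacologist and a statistician. Section 10.5 has a panel of three psychiatrists look after two administrations, and then: "This analysis will be repeated after a total of 20 psilocybin administrations have been completed".

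**The concern.** The primary objective (section 4.1) is safety and tolerability in adolescents as well as young adults. The amount of adult experience required before anyone aged 16-17 is exposed is the main staged protection that the protocol describes for them.

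That condition is stated in two ways that differ by a factor of about two in dosed adults, and the stricter one asks for more dosed adults than the psilocybin arm has places. A site that follows section 10.5 would never open recruitment to minors, and the adolescent part of the primary objective would go unanswered. A site that follows the synopsis would open it after about half the adult dosing experience that section 10.5 states. An ethics committee or regulator reading only one of the two passages would misjudge what has been promised.

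**Working it through.** **Inputs.** 40 participants, 20 per group (synopsis, section 10.4); 1:1 allocation in blocks within age strata, block size not given (section 5.1); two sessions per psilocybin participant (section 5.1); 25 adults then 15 minors (synopsis); 25 adults dosed (section 10.5).

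**1. The plan's own figures.** 40 × 1/2 = 20 per group, as stated. 25 + 15 = 40, as stated. Sessions in the randomised trial: 20 × 2 = 40.

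**2. The section 10.5 condition against that size.** 25 − 20 = 5 more dosed adults than the whole arm. If all 40 participants were adults, 1:1 blocks would give 20 dosed (at most 21 for even block sizes from 2 to 10).

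**3. Size that the section 10.5 condition needs.** Adults to randomise: 25 / 0.5 = 50. With 15 minors: 50 + 15 = 65, of whom 32-33 would be dosed. With an assumed pre-dose loss of 10% or 20%, the adults needed become 50 / 0.9 → 56 or 50 / 0.8 → 63.

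**4. What the synopsis condition delivers.** 25 × 0.5 = 12.5, so 12-13 dosed adults (at most 15, with blocks of 10) and about 24-26 adult sessions. Minors: 15 × 0.5 = 7.5, so 7-8 dosed.

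**5. What each condition can rule out.** If no event of a given kind is seen in n dosed adults, the one-sided 95% upper limit on its risk is 1 − 0.05^(1/n):

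| Dosed adults | Upper limit |
|---|---|
| 12 | 22.1% |
| 13 | 20.6% |
| 25 | 11.3% |

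**6. Whether the switch closes the gap.** With 25 adults, 13 on psilocybin and 12 on control, and a share u of controls switching, the number ever dosed is 13 + 12u: 25 at u = 1, 23.8 at 0.9, 22.6 at 0.8 and 19 at 0.5. So 25 is reached only if essentially every adult control switches. Recruiting more adults eases this but uses up the minors' places: with all 40 places adult, 20 + 20u passes 25 at u = 0.25, and no minor can then be enrolled.

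The calendar is also tight. Q3 2025 to Q2 2027 is at most 24 months, and participation lasts 52 weeks, so the last minor must start by about month 24 − 12 = 12. A switching control must first complete six months, so the last of the 25 adults would have to start by about month 12 − 6 = 6, and somewhat earlier once the preparation and dosing weeks are counted.

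**7. Review points.** Section 10.5: after 2 and 20 administrations. Section 9.5: after 10, 20, 30 and 40 sessions, plus quarterly. Synopsis: after the first 10. All of 2, 10, 20, 30 and 40 fall within the 40 sessions, so they differ from one another but can all be held.

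**8. The 40 against the floor of 20 dosed.** At assumed pre-dose losses of 5%, 10% and 20%, dosing 20 needs 20 / 0.95 → 22, 20 / 0.9 → 23 and 20 / 0.8 → 25 per arm, or 44, 46 and 50 randomised.

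**The case against.** **Loose wording.** The strongest defence is that section 10.5 simply means 25 adults enrolled. The synopsis figures add up to 40 and fit 1:1 allocation, so the conflict sits in one sentence. But sections 5.1 and 10.1 take care to separate participants who are dosed from those who are only randomised, so a reader has no licence to treat the two as the same in section 10.5. That the conflict is confined to one sentence makes it cheap to repair; it does not remove it.

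**The 20 dosed is a floor.** This is correct, and one should not infer that the trial closes once 20 are dosed; recruitment may go further. Getting to 25 dosed adults still takes about 50 randomised adults, which no section provides for.

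**The switch.** It is true that people outside the randomised psilocybin arm may be dosed later. No section counts them towards the entry condition, and the route works only at near-complete uptake if 15 places are kept for minors.

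**Reviews and size targets.** A reader might infer that the review points are also impossible at this size, or that sessions in minors would have no event-triggered review. Neither is supported. The schedules can all be held together. The second inference joins section 10.5's review points to the synopsis's entry condition and ignores section 9.5, which keeps reviews at every 10 sessions and quarterly. Nor does the synopsis say that its review after 10 sessions is the only one. A reader might also see three rival sample sizes, but sections 5.1 and 10.1 already say that recruitment continues until 20 are dosed, and "design in up to 40 completing patients meeting DSM-5 criteria for eating disorders" in section 10.2 reads as a loosely worded ceiling.

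**Conclusion.** The point stands for the entry condition. Section 10.5 sets a threshold of 25 dosed adults that a 1:1 trial of 40 cannot reach within its randomised part (about 20 dosed), and the synopsis sets a different one that yields 12-13 dosed adults. The gap is a factor of about two in adult dosing experience (12.5 / 25), or an upper limit of about 21-22% against 11% for an event not yet seen. Keeping the section 10.5 figure would mean about 65 participants instead of 40. These results rest on the stated total and allocation ratio. They assume no pre-dose loss, which would only widen the gap, and that switched controls do not count, since nothing says that they do.

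Because this condition governs when minors are exposed and whether the adolescent part of the primary objective can be addressed, it needs correcting before recruitment relies on it.

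Two lesser points go with it. The review timings and reviewing bodies differ between the synopsis, section 9.5 and section 10.5, without clashing with the trial size. And the 40 is exact only if nobody is lost before dosing.

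**What to change.** Reconcile section 10.5 with the synopsis and with sections 5.1, 10.1 and 10.4. State one entry condition for 16-17-year-olds as a number of dosed adults, and make the size agree with it, either by choosing a number that the stated design delivers or by restating the total to match the number chosen. Say whether controls who switch count towards it. Which entry rule is right is for the sponsor to decide and justify.

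In the same amendment:
- Give one list of safety-review points and name one reviewing body, consistently in the synopsis, section 9.5 and section 10.5.
- Describe 40 as approximate in the synopsis and section 10.4, since recruiting until at least 20 are dosed takes the randomised number above 40 whenever someone is lost before dosing.

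The cost is a protocol amendment to the text. No extra participants are needed for the entry condition unless the sponsor keeps 25 dosed adults, in which case the total rises to about 65 before any pre-dose loss.

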***Halt and/or Early Termination Criteria***

Halt and/or Early termination may be initiated if any of the following occurs:

- Unacceptable or unforeseen safety concerns, including unexpected serious adverse reactions (SUSARs) or a pattern of adverse events suggesting increased risk.
- Insufficient recruitment, defined as fewer than 30% of the planned number of participants being enrolled within 18 months of trial initiation.
- Emerging external evidence (e.g. from other clinical trials or meta-analyses) indicating that the investigational product poses a significant safety risk or is no longer ethically justifiable to study.
- Ethical concerns raised by the Safety Review Committee, monitor oversight or regulatory authorities.
- Withdrawal of essential approvals, resources, or study drug availability.

In the event of early termination or temporary halt, all relevant regulatory authorities (including CTIS, Läkemedelsverket, and EPN) will be notified within 15 calendar days, as per applicable regulations. The reason for halt and/or early termination will be documented and explained in the final report.

Safety Review committee and monitor clearance will be required before resuming after a temporary halt not leading to and early termination.

- End of the Clinical Trial: When the last participant completes the last follow-up visit at week 52.

6. Subject Selection

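### Recruitment of 16-17-year-olds opens on a count of adults, with no safety review or committee clearance stated as a condition for that step

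*Protocol*

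**What the plan says.** Section 10.5 (Interim Analysis) ends with the rule: "After 25 patients over 18 have been through dosing sessions, patients 16-17 will be recruited". The synopsis, under Ethical Considerations/Benefit-Risk, has: "First 25 participants included above 18 years of age, followed by 15 patients between 16-17 years of age". One counts adults dosed and the other adults included, but in both the only input is a count.

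The surrounding oversight is as follows.

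- **Section 10.5, panel looks.** "Following two administration sessions of 25mg psilocybin, a panel of three senior psychiatrists, who are not part of the research team, will conduct an evaluation". Its subject is safety and protocol adherence. Then: "This analysis will be repeated after a total of 20 psilocybin administrations have been completed". Neither look is linked to the opening of the younger group.
- **Section 9.5.** The Safety Review Committee reviews safety data each quarter and after every 10 dosing sessions, and hears of all serious adverse events within 24 hours. On its powers: "They may recommend protocol modifications, halting recruitment, or terminating the trial based on emerging risks".
- **Section 5.4.** The general statement says that a temporary halt or early termination will occur if significant concerns arise from the sponsor, the monitoring oversight or the committee. The criteria list beneath it is softer: "Halt and/or Early termination may be initiated if any of the following occurs". It names a pattern of adverse events suggesting increased risk as one ground. It adds: "Safety Review committee and monitor clearance will be required before resuming after a temporary halt".
- **Section 7.4.** Control participants may switch to psilocybin only after the safety committee has found safety and preliminary efficacy satisfactory. Section 5.1 says much the same.

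**The concern.** Adults are recruited first so that what is seen in them can inform whether minors are exposed. The synopsis lists the sequence among the ethical and benefit-risk measures, so it is offered as a safeguard. As written, it delays the exposure of minors but does not require anyone to decide, on the adult data, that the exposure should begin.

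This matters most when the adult experience is equivocal: events that call for deliberation but that nobody has yet raised as a significant concern. With a required clearance, the committee would have to look and record a view before the first 16-17-year-old is recruited. Under the present wording, recruitment moves on if nothing is said.

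**Working it through.** The question is whether any stated review or clearance is a condition of opening recruitment at 16-17. It is settled mainly by reading the provisions side by side.

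**Step 1. What each step in the protocol requires**

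| Step | Stated condition | Committee decision required first? |
|---|---|---|
| Open recruitment at 16-17 (10.5) | 25 adults through dosing | No |
| Same step (synopsis) | 25 adults included | No |
| Resume after a temporary halt (5.4) | Clearance by committee and monitor | Yes |
| Control participants switch to psilocybin (7.4) | Six-month follow-up and a safety committee determination | Yes |

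The protocol states a committee decision as a condition in two places. It does not do so for the first exposure of minors.

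**Step 2. Whether a scheduled review falls at the step anyway**

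Inputs: two doses per participant and 1:1 allocation (5.1); panel looks at 2 and 20 administrations (10.5); committee reviews every 10 sessions (9.5).

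- *25 adults dosed (10.5).* If all receive both doses, 25 × 2 = 50 sessions. Committee reviews fall at 10, 20, 30, 40 and 50 sessions, plus quarterly. The last coincides with the count, but only by arithmetic: the text does not make opening wait for it. The last panel look, at 20 administrations, is well past.
- *25 adults included (synopsis).* At 1:1, 25 × 0.5 = 12.5, so about 12 or 13 adults allocated to psilocybin and about 12.5 × 2 = 25 sessions once all have had both doses. Session-count reviews fall at 10 and 20, plus quarterly. Inclusion precedes dosing, so fewer than 25 sessions may have taken place when the count is reached.

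On either reading the committee will have seen adult data before the younger group opens. On neither is a review at that point required, or its outcome made a condition.

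**Step 3. What happens by default**

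There are two routes by which adult data could stop the step: a halt under 5.4, or a committee recommendation to stop recruitment under 9.5. Both need someone to act. If nobody does, the count opens recruitment. No provision requires a positive decision.

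**The case against.** The strongest reply is that oversight is already substantial and partly mandatory. The general statement in 5.4 says a halt will follow significant concerns, and after a temporary halt recruitment cannot resume without clearance. The committee can also recommend stopping recruitment alone. Serious adverse events reach it within 24 hours, so it need not wait for a scheduled look. Section 12.3 adds parental or caregiver consent and age-appropriate information for those aged 16-17. All of this stands.

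It also defeats two stronger readings. A reader might infer that minors would be recruited whatever happened in adults, or that the protocol cannot tell a safe adult experience from an unsafe one. The documents do not support that: it follows only if the halt route is assumed away, and that route is how adult data act. A reader might also want to size the problem by the chance that a given risk produces no event among the few adults dosed. That chance reflects how few adults are dosed. It would be unchanged if a clearance were added at the same count, so it does not measure this gap.

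It could also be said that the switch in 7.4 is a different kind of step, because it changes an allocated treatment. That is fair, but the contrast remains: a control participant, adult or not, needs a committee determination before receiving psilocybin, and the start of recruitment at 16-17 needs none.

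What the reply does not supply is a review tied to this step.

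**Conclusion.** The point holds in a limited form. Adult safety data are reviewed and can stop the trial, but recruitment at 16-17 proceeds unless halted; it does not wait to be cleared. That is a weaker condition than the protocol sets for the control-arm switch or for resuming after a halt.

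No probability is attached, because any figure would rest on assumed event rates and on how often the halt powers are used, and the documents give neither. The conclusion rests on the wording of 10.5 and the synopsis, read with 5.4, 7.4 and 9.5.

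It does not depend on which reading of 25 is right. Whether 25 means included or dosed, and how 25 dosed adults fits 20 per group, is a separate matter to reconcile. So are the differing review schedules in the synopsis, 9.5 and 10.5. Correcting either would still leave a count with no clearance attached. The change should be made, but the existing halt powers keep this from being a critical defect.

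**What to change.** Reword the last sentence of 10.5 and the matching sentence of the synopsis so that recruitment of 16-17-year-olds opens only when both conditions are met: the adult count has been reached, and the Safety Review Committee has reviewed the accumulated safety data of the dosed adults at that point and recorded a recommendation to open. The clinical criteria for that recommendation are for the committee to set; none is proposed here.

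The cost is one sentence in two places and one recorded decision by a committee that already meets quarterly. The downside is a possible short delay before the younger group opens.
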